### Study setting

Programme content is delivered by the intervention facilitator, that is, group leader via synchronous online sessions. Between sessions, participants will be asked to complete assignments in their home environment. The assignments are designed to encourage participants to practise skills learnt during the intervention, that is, to carry out their individual action plans. The participants and intervention facilitators may be located anywhere in Sweden.

### Recruitment and procedures

Participants will be recruited via flyers placed in inpatient and outpatient MS and rehabilitation clinics, from social media advertisements published by Karolinska Institutet, and by the patient organisation Neuro Sweden.

The notices will include a link to a webpage with study information and an online template where interested individuals can fill in their contact information. A research assistant with training in Good Clinical Practice^30^ will screen the completed templates regularly, contact potential participants by phone or e-mail (depending on PwMS’ choice of contact), and provide potential participants with information about the study. Individuals expressing interest in the study will be screened for eligibility. The informed consent process will be initiated with PwMS who meet the eligibility criteria. Specifically, eligible PwMS will be sent written information. Informed consent (online supplemental material) is obtained through BASS, an integrated online treatment and assessment platform. The platform is provided by the eHealth Core Facility at Karolinska Institutet, Stockholm, Sweden. Individuals providing informed consent will be included.

Baseline assessment will be supported by the use of the BASS database. The PwMS will subsequently be randomised to the intervention group or the control group using a data-generated system (Sealed Envelope Ltd. 2021). Participants will be stratified as non-ambulatory (able to walk a maximum of 5 m with assistance or not able at all) or ambulatory in a 1:1 allocation ratio of blocks of eight. Participants will be contacted by phone to inform them about group allocation.

Recruitment began in December 2023, and the expected completion of the study is January 2027. An overview of the study schedule of enrolment, allocation, intervention and assessments are presented in figure 1.

### Control

Participants allocated to the control group will receive a brochure about fall risk factors and fall prevention for PwMS in addition to their standard MS care and rehabilitation.

### Intervention

The intervention group participants will receive (a) the same brochure about fall risk factors and fall prevention strategies for PwMS provided to the control group participants, (b) the opportunity to participate in the *Fewer Falls* programme and (c) their standard MS care and rehabilitation. The manualised *Fewer Falls* programme features self-management content created to enhance the participant’s ability to manage fall risks in everyday life. The intervention is considered a complex intervention^22^ as it includes multiple components, behaviours, expertise and skills both by PwMS and group leaders and permits flexibility in its components. Through *Fewer Falls*, participants learn to (a) identify their fall risk, (b) make own action plans and follow out the planned activities, (c) be aware of their capacity in relation to expectations and demands in daily life, (d) to follow-up on the action plan and (e) know about behavioural change and how to sustain their motivation to prevent falls.

The manualised intervention consists of eight online synchronous (Zoom Video Communications) sessions: seven 2-hour sessions conducted weekly, and one 2-hour booster session conducted 4 weeks after the seventh session. The participants will receive home assignments to perform between the sessions. The assignments are designed to encourage participants to practice skills learnt during the intervention, ie, to carry out their individual action plans. Each session has the following structure: check-in, follow-up on home assignments, interactive presentation with discussions in smaller groups and/or the whole group, introduction to home assignment and check-out (table 1).

**Table 1 T1:** Main topic and activities of *Fewer Falls*

Session*/Home assignment#	Main topics and activities
Session 1: Acquaintance with group, programme and technique.	Check-in.Presentation: Programme overview.Presentation/Discussion: How to use the online platform, get to know each other and build trust.Check-out.
Home assignment 1.	Participants post a short introduction on the online platform (BASS).
Session 2: Falls in MS.	Check-in.Discussion: Group consensus on group interaction.Interactive presentation: Why do people with MS fall?Presentation: Introduction to the action plan to prevent falls.Interactive presentation: New behavioursCheck-out.
Home assignment 2.	Participants take a photo of a fall hazard they want to address and describe how the image in the photo presents a fall risk. Start individual action plan no. 1.
Session 3: My fall risks.	Check-in.Follow-up: Discussion on each other’s fall risks.Interactive presentation: Environmental fall risks. Working with action plan no. 1.Check-out.
Home assignment 3.	Participants carry out activities planned in individual action plan no. 1.
Session 4: Behavioural change.	Check-in.Follow-up: Evaluation of action plan no. 1.Interactive presentation: Behavioural change to prevent falls including supportive and hindering factors related to falls prevention behaviour change.Start of writing action plan no. 2.Check-out.
Home assignment 4.	Participants evaluate action plan no. 1 and complete the writing of action plan no. 2 and start the planned activities.
Session 5: Thoughts and emotions and fall risk.	Check-in.Follow-up: Presentation of and reflection on action plan no. 2.Interactive presentation: How can thoughts and emotions affect the risk of falling?Check-out.
Home assignment 5.	Participants carry out activities planned and evaluate action plan no. 2.
Session 6: Physical symptoms and fall risk.	Check-in.Follow-up: Evaluation of action plan no. 2.Interactive presentation: Physical factors related to fall risks and how these risks can be reduced.Start of writing action plan no. 3.Check-out.
Home assignment 6.	Participants complete the writing of action plan no. 3 and start the planned activities.
Session 7: Aids to reduce fall risk.	Check-in.Follow-up: Evaluation of action plan no. 3.Interactive presentation: How can aids reduce fall risk?Interactive presentation: Behaviour changes and maintenance.Check-out.
Home assignment 7.	Participants carry out and evaluate action plan no. 3. Write, carry out and evaluate action plan no. 4. Declaration of interest to stay in touch.
Session 8: Booster session.	Check-in.Follow-up: Evaluation of action plan nos. 3 and 4.Programme evaluation.Check-out.

* Group leader led synchronous online group- sessions, #individual home- assignments between sessions.

The intervention is delivered to groups of approximately eight participants. A health professional (ie, a physiotherapist, occupational therapist or social worker) recruited via the researchers’ network facilitates the online synchronous group sessions. Seven group leaders will be recruited to lead one or two cycles (ie, seven sessions followed by one booster session) of the programme in concurrently ran groups. The research team recognise the importance of involving several group leaders to allow for effective assessment of programme fidelity and reduce the possibility that successful programme outcomes would be attributed to the skill set of one or two group leaders. Approximately 15 cycles of the *Fewer Falls* programme will be run. The group leaders will not be involved in the usual care of the participants.

The group leaders will complete an extensive online training programme before delivering *Fewer Falls*. This training programme will consist of asynchronous online modules. Collectively, these modules (a) describe the aim, structure, content and theoretical foundation of *Fewer Falls* as well as the role of the group leaders; (b) provide an overview of MS, falls and fall risk factors for PwMS; (c) orient group leaders to the *Fewer Falls* group leader manual; and (d) provide detailed descriptions of content and process of *each programme* session. Each module of the training programme ends with a quiz or a reflective question. The final module of the training programme consists of a synchronous online role-play session. In addition, the group leaders will receive instructions on how to use the digital tools used during the *Fewer Falls* programme.

To ensure participant adherence to the programme, the group leaders will contact participants who missed one session. If participants miss two sessions in a row, the research assistant will contact the participants.

### Theoretical basis, self-management approach and pedagogical model

The leading theory informing the *Fewer Falls* programme content and process is the Social Cognitive Theory (SCT).^31 32^ Reciprocal determinism, the central concept of SCT, refers to the dynamic and reciprocal interaction of person (with learnt experiences), environment (external social context) and behaviour (responses to stimuli to achieve goals).^32^ Reciprocal determinism is applied in *Fewer Falls* because participants, with their respective experiences, work together to learn about fall risks and management strategies and change their behaviours to reduce their risk of falling. The SCT components of observational learning and reinforcements align well with the programme’s focus on group format; participants are learning and receiving feedback from peers. According to SCT, self-regulation refers to the ability to understand and manage own behaviours.^32^ In *Fewer Falls*, self-regulation supporting the reduction of fall risk is fostered through using two to four action plans. Through each action plan, participants identify and explain a specific fall risk, a strategy to address that fall risk, their level of confidence in implementing that strategy, the deadline for completion and resources to support their success in implementing the strategy. Each action plan includes a section for participants to evaluate the extent to which the planned strategy was implemented. Participants are given the opportunity to report on the status of their action plans and work together to refine action plans as needed. Self-efficacy, a central component in SCT, is described as a possible mechanism by which self-management is achieved.^33^ An important goal of *Fewer Falls* is to build participants’ falls self-efficacy.

Lorig and Holman’s operationalisation of self-management^33^ was carefully applied to develop *Fewer Falls*. Specifically, the programme includes discussions about self-management tasks: medical management of MS symptoms that can reduce fall risk; role management, for example, PwMS’ role as partner, parent and/or employee; and emotional management with emphasis on thoughts and emotions in relation to falls. The depth and focus of the discussions are dependent on participants’ interests/priorities (eg, identified fall risks) and experiences. Lorig and Holman described six self-management skills, all of which are included in *Fewer Falls* to foster participants’ ability to manage fall risks in daily life: problem solving, decision making, resource utilisation, patient-provider partnership, self-tailoring and the aforementioned action planning.

SCT is complemented by the Transtheoretical Model (TTM) for behaviour change^34^ as a theoretical basis for *Fewer Falls*. TTM is primarily applied through an interactive discussion led by the group leaders on the six phases of health behaviour change (precontemplation, contemplation, preparation, action, maintenance of behaviour and relapse) that participants may experience as they learn to use action plans to prevent falls.

To guide the online learning component of *Fewer Falls,* the Salmon 5 Stage Model was utilised because it was specifically developed to support e-learning in groups.^35^ The model consists of five stages: (1) access and motivation, (2) online socialisation (team building), (3) information exchange, (4) knowledge construction (critical thinking) and (5) development (review and responsibility for own learning). The amount of interactivity is increased in each stage of the model. The model stresses the importance of group leaders acting as moderators/facilitators of online discussions. In the early stages of the programme, group leaders support participants’ motivation and engagement with the rest of the group. The model also recommends that facilitators taper off their leadership as the course progresses, allowing space for greater peer support and peer learning.^35^ The application of the model as used in *Fewer Falls* is presented in figure 3.

**Figure 3 F3:**
[figure not shown]
The five-stage model as applied in *Fewer Falls*

### Data collection and outcome measures

#### RQ 1a, RQ 1b and RQ 2: effectiveness study

Data will be collected using the digital platform BASS database. The data collection will be blinded as the participants receive a link to the BASS database, which provides them with access to the questionnaires that are completed online. Baseline data includes the sociodemographic information (ie, age, sex, civil status, work status and educational level); disease-related characteristics (ie, MS severity, time since diagnosis, symptoms, medications and other treatments, other diagnosis and aids); formal/informal care; cognitive function (collected through the short version of the Montreal Cognitive Assessment Scale^36^); anxiety and depression (collected through the Hospital Anxiety and Depression scale^37^); fatigue (assessed by the Fatigue Severity Scale^38^); health literacy (assessed via the Swedish version of the Health Literacy Survey European Questionnaire/16 item version^39^); self-reported falls and fall related injuries in the previous 6 months; and expectations on the programme.

The primary outcome of *Fewer Falls* is fall frequency.^40^ The primary endpoint is 6 months after the start of the intervention. However, falls will be monitored in both intervention and control groups from the start of the *Fewer Falls* programme until 12 months after the start of intervention, as recommended in fall prevention literature.^41^ An online SMS will be sent to the intervention and control participants once a week asking, ‘Have you fallen within the last week?’ The total number of falls, number of fallers and injurious fall incidence^40^ will be recorded. Participants answering ‘yes’ to the weekly SMS will receive a questionnaire through BASS that includes a series of questions about fall-related injuries. A fall is defined as ‘an unexpected event in which the participants come to rest on the ground, floor or lower level’.^41^ Secondary outcomes, collected at baseline and 3, 6 and 12 months after the start of intervention, are sense of control of falls prevention assessed by the Falls Control Scale^42^ (administered to all participants), a direct measure of fear of falling^43^ and falls self-efficacy assessed by the Short Falls Efficacy Scale-International^44^ (administered to ambulatory participants), the Spinal Cord Injury Falls Concern Scale^45^ (administered to non-ambulatory participants) and a revised version of the Short Falls Efficacy Scale-International^46^ (administered to all participants). The following are also administered to all participants to collect data: activity curtailment assessed by a single question,^43^ perceived impact of MS assessed by the Multiple Sclerosis Impact Scale^47^ and self-rated health assessed by the EuroQol-5D-5L.^48^

Participants who discontinue the intervention will be contacted and asked if they are willing to continue responding to the SMS and questionnaires.

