### Analysis

#### Data management and statistical methods

##### RQ 1a, RQ 1b and RQ 2: effectiveness study

Intention-to-treat and per-protocol analyses will be performed. Per-protocol analyses will include participants who fulfil content adherence, defined as completion of at least two action plans.

Descriptive statistics will be used to present data, for example, means, medians, frequencies, SD, quartiles and counts. Drop-out analyses of baseline characteristics will be explored with parametric and non-parametric analyses depending on the data level.

The primary analysis for falls (falls/person/year) will be conducted using generalised linear mixed models (GLMM) with a Poisson link function to account for count data distribution and potential overdispersion. The model will include fixed effects for the intervention group and random effects for participant variations over time. Interactions between variables will be included if deemed necessary. Linear mixed model analyses will be used for normally distributed secondary outcomes. For categorical outcomes, GLMM with logistic or ordinal regression will be used, depending on the nature of the outcome (binary or ordinal). The primary endpoint is 6 months after the start of the intervention. In addition, analyses of sustainability of potential effects will be performed after 12 months. Any missing data will be handled using appropriate methods, such as multiple imputation, to ensure robustness in analyses. Analyses will be performed and reported in accordance with the Consolidated Standards of Reporting Trials (CONSORT) guidelines for RCT.^50^ A data management plan is established and stored at the Research Data Office at Karolinska Institutet.

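### Follow-up after stopping the programme is tied to renewed willingness, a trigger only the intervention arm can meet, so the intention-to-treat comparison risks differential missing outcome data

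*Protocol article*

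**What the plan says.** Under Data collection and outcome measures (RQ 1a, RQ 1b and RQ 2), the article sets up the same falls monitoring in both arms: "falls will be monitored in both intervention and control groups from the start of the" programme until 12 months, with the primary endpoint at 6 months. The instrument is a weekly text message: "An online SMS will be sent to the intervention and control participants once a week asking" about falls in the past week. The same section closes with the rule at issue: "Participants who discontinue the intervention will be contacted and asked if they are willing to continue responding to the SMS and questionnaires".

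Under Control: "Participants allocated to the control group will receive a brochure about fall risk factors and fall prevention for PwMS", on top of standard care. Only the intervention arm has sessions. Under Intervention, group leaders contact anyone who misses one session, and then: "If participants miss two sessions in a row, the research assistant will contact the participants".

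Under Analysis (Data management and statistical methods): "Intention-to-treat and per-protocol analyses will be performed". On incomplete data: "Any missing data will be handled using appropriate methods, such as multiple imputation, to ensure robustness in analyses". And: "Drop-out analyses of baseline characteristics will be explored with parametric and non-parametric analyses depending on the data level".

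**The concern.** An intention-to-treat comparison needs the fall count of every randomised person, whether or not they stay in the programme. The rule makes leaving the programme an occasion to ask whether the person will also go on supplying outcome data. That occasion is defined by discontinuing the intervention, so it cannot arise for a control. The arms therefore differ, by design, in one route out of the primary outcome, and in the intervention arm that route is linked to non-adherence.

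Non-adherence could be related to falling. The Introduction names impaired cognition among the fall risk factors and says that the online format was chosen with low energy levels in mind. The Discussion says that the programme is aimed at people with the technical and cognitive ability for a complex intervention. People who stop may therefore fall at a different rate from those who stay. If they also leave follow-up more often than comparable controls, the two observed groups are no longer the two randomised groups.

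Timing adds to this. Seven weekly sessions and a booster four weeks later end at about week 11, so stopping happens early in the 6-month window. Someone who stops at week 11 and declines loses 26 − 11 = 15 of 26 primary-outcome weeks, or 58%. Someone who stops sooner loses more.

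**Working it through.** The article gives no figure for loss after discontinuation, so there is none to reproduce. The steps below show only what the rule could do under stated assumptions.

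**Inputs**
- Up to 35% drop-out and 240 recruited 1:1, so 120 per arm (Participants; Recruitment and procedures). The 35% is for the whole trial and is not split by arm. Using it as the share of the intervention arm that stops (0.35 × 120 = 42) is an assumption at the upper end.
- Planning ratio from the pilot: 2.45/3.69 = 0.66 (Participants), for scale only.
- Assumed: *h*, the fall rate in stoppers relative to completers, from 0.5 to 2; *d*, the share of stoppers who decline further follow-up; no true effect; no loss among controls.

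**Formula.** With completers at rate 1, the full intervention-arm mean is 0.65 + 0.35*h*. If decliners contribute nothing, the observed mean is [0.65 + 0.35(1 − *d*)*h*] / [0.65 + 0.35(1 − *d*)]. The apparent rate ratio is observed mean divided by full mean.

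**All stoppers decline (*d* = 1).** The observed mean is 1.
- *h* = 2: 1/1.35 = 0.74
- *h* = 1.5: 1/1.175 = 0.85
- *h* = 1: 1/1 = 1.00
- *h* = 0.5: 1/0.825 = 1.21

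**Half decline (*d* = 0.5).**
- *h* = 2: (0.65 + 0.35)/0.825 = 1.212; 1.212/1.35 = 0.90
- *h* = 1.5: (0.65 + 0.2625)/0.825 = 1.106; 1.106/1.175 = 0.94
- *h* = 0.5: (0.65 + 0.0875)/0.825 = 0.894; 0.894/0.825 = 1.08

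**Weeks before stopping are kept.** Take the latest stopping point, week 11 of 26, with all stoppers declining and a pooled rate per person-week. Completers supply 0.65 × 26 = 16.9 weeks and stoppers 0.35 × 11 = 3.85, in total 20.75.
- *h* = 2: (16.9 + 7.7)/20.75 = 1.186; 1.186/1.35 = 0.88
- *h* = 0.5: (16.9 + 1.925)/20.75 = 0.907; 0.907/0.825 = 1.10

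Earlier stopping lies between these values and those for *d* = 1.

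**Equal loss in both arms.** If controls lose the same share with the same *h*, numerator and denominator shrink by the same factor and the ratio is 1.00.

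A distortion therefore needs two things together: more loss in one arm, or loss of a different kind, and a fall rate in those lost that differs from that in those retained. The documents give neither quantity.

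**The case against.** The strongest reply is that the sentence is a retention step. It seeks to keep data from people who leave the programme, which is what intention-to-treat requires. Nothing says that messages stop at discontinuation, that silence counts as withdrawal, or that later data are excluded. Controls can also stop replying, and the additional contact might improve retention in the intervention arm. All of this stands. A reader might infer that data are lost selectively and that the comparison is biased in favour of the programme. The documents do not support that: they show no loss, and stoppers who fall less would push the result against the programme.

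It can also be said that reminder procedures for unanswered messages are operational detail that an article leaves to the full protocol, and that the missed-session contacts serve programme adherence and not data collection. Both points are fair. The absence of a stated reminder rule for controls is not part of this point. Nor can it be shown that participants have already agreed to a full year of messages, because the consent form is not in view.

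Finally, multiple imputation can use arm, action plans and the baseline measures of fatigue, cognition and previous falls. Where those explain the loss, imputation can deal with it, and its details may sit in an analysis plan not shown. It remains that usual imputation does not repair loss that depends on falls never reported, and that no analysis plan can collect them afterwards. The rule at issue governs conduct and is stated in the article itself.

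**Conclusion.** The point holds as a risk. The article ties continued follow-up after stopping the programme to a renewed expression of willingness, and only the intervention arm can meet that trigger. This sits badly with the promised intention-to-treat analysis.

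Size and direction are unknown. The extreme range under no true effect, 0.74 to 1.21, requires 35% of the intervention arm to stop, every one of them to decline, no weeks kept, no control loss, no adjustment, and a relative fall rate between 2 and 0.5. If half decline, the range is 0.90 to 1.08. The lower extreme would not be trivial beside the planning ratio of 0.66, but nothing in the article makes it likely. The case for change is that the ambiguity is cheap to remove now and cannot be undone after data collection.

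**What to change.** Replace the sentence with an arm-neutral rule, for example: *Stopping the programme does not end follow-up. Weekly SMS and the 3, 6 and 12 month questionnaires continue by default for all randomised participants for 12 months, unless the participant withdraws from data collection.*

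Let the same event, such as an unanswered SMS or questionnaire, trigger reminder contacts in both arms. If the full protocol already has such a rule, refer to it here. Record programme discontinuation and withdrawal from data collection as separate events, and report both by arm.

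The cost is protocol wording, possibly a setting in the message system, and some extra reminders by the existing research assistant. Some people who have left the programme will go on receiving messages until they opt out.
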